### Inclusion criteria

Participants with clinic blood pressure more than or equal to 130/80 mmHg who are not taking medicationParticipants with controlled blood pressure defined as < 130/80 using antihypertensive medication for a minimum of 6 weeksParticipants live in Banshgram Union only

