**Methods:**

A single-center cluster randomized controlled trial (RCT). The study will be conducted for 6 months, a total of 300 participants of age 30 to 75 years with 150 adults in each of the intervention and the control arms. The intervention arm will involve the delivery of a blended learning education program on lifestyle changes for the management of high blood pressure. The education program comprises evidence-based information with pictures, fact sheets, and published literature about the effects of high blood pressure on CVD development, increased physical activity, and the role of a healthy diet in blood pressure management. The control group involves providing information booklets and general advice at the baseline data collection point. The primary outcome will be the absolute difference in clinic SBP and DBP. Secondary outcomes include the difference in the percentage of people adopting regular exercise habits, cessation of smoking and reducing sodium chloride intake, health literacy of all participants, and the perceived barriers and enablers to adopt behavior changes by collecting qualitative data. Analyses will include analysis of covariance to report the mean difference in blood pressure between the control and the intervention group and the difference in change in blood pressure due to the intervention.

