### Aim of the study

The aim of this study is to investigate if a health education intervention program lowers high blood pressure.

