### Participants

The study will be conducted in the Banshgram Union of Narail district, located approximately 200 km southwest of Dhaka, Bangladesh. To understand the location, Bangladesh is a country of over 163 million people divided into 64 districts. Each district is divided into Upazilas (sub-districts), and each Upazila is divided into Unions which consist of 15–20 villages [37]. A cross-sectional study was conducted among 3104 participants of age 30–89 years in 2013 in the Banshgram Union that identified 1242 (40%) participants with hypertension according to WHO guidelines as SBP ≥140 mmHg and/or DBP ≥90 mmHg and/or self-report use of medication for hypertension [15]. Given the intervention of the present study that needs lifestyle modification and more use of a mobile phone, it was decided to limit the age to 75 years as access and use of mobile phones was likely more problematic with older participants [38]. Thus, we chose to limit our upper age to 75 years, leaving 1072 eligible participants for this study. Based on power calculations, we require only 300 participants and expect to recruit the required number of participants without any major difficulty. Inclusion criteria will be based on recent guidelines or definition of hypertension [25]; anyone with SBP ≥130 mmHg and/or DBP ≥80 mmHg and/or self-report use of medication for hypertension will be considered eligible for the current study.

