### Recruitment

Recruitment will be conducted by the investigators of the Organization for Rural Community Development (ORCD) in Bangladesh (www.orcdbd.org). The ORCD is a local non-government organization involved in providing health services to rural people and conducting research. The ORCD investigators, and trained data collectors, will communicate with the potential participants over the telephone or by direct contact. The ORCD participants are not involved in the study design, but they will be involved in the recruitment and conduct of the study. Upon establishment of contact with eligible participants, the baseline data collection will be done through household visits. At household visits, the ORCD investigators and the data collectors will briefly explain the study objectives and their voluntary participation in the project. Interested potential participants will be assessed for eligibility that includes the measurement of blood pressure. Informed written consent will be obtained from all participants. Upon enrolment, a face-to-face interview will be conducted to collect information and record blood pressure from the participants whilst maintaining a social distance. Recruitment will stop once the required number of participants are enrolled. If we are unable to recruit completely from the original cohort, we will expand and recruit participants from outside of this specific cohort but from the exact location. Recruitment from outside of the proposed cross-sectional cohort is not expected to affect the primary objectives. Our source population is over 1000 participants. We do not anticipate any problems in recruiting 300 participants.

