### Equipment and blood pressure measurements

Blood pressure will be measured using a calibrated Omron Premium Blood Pressure Monitor Device, Omron HEM-7322 (Australia). Blood pressure will be measured from the right arm with the person sitting upright after 3 min of rest, and a further measurement will be taken following a period of at least 3 min of rest. A third measure will be taken if a major difference is observed between the first two measures and the nearest two measures will be recorded. The two readings will be averaged for SBP and diastolic blood pressure (DBP) separately. Participants will be considered to have high blood pressure if recorded SBP ≥130 mmHg and/or DBP ≥80 mmHg.

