### Outcome measures

#### Primary outcome

The primary outcome is the difference in clinical SBP and DBP within and between control and intervention groups. We will report both the absolute difference and the difference in change after follow-up.

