### Statistical analyses

Although the intervention will be conducted as clusters, data will be collected as individuals within clusters and the effect of the intervention will be measured based on individual’s data. Since the randomization is based on clusters, there might occur differences in baseline characteristics of participants. The baseline characteristics for the intervention and the control group will be examined using the chi-square test or Fisher’s exact test for categorical variables and the two-sample *t-*test or Mann-Whitney U test for continuous variables depending on the distributions of the data.

The effect size will be the mean difference in the primary outcome. The comparison will be made between differences for control and intervention groups after the follow-up. More specifically, it could be shown as the difference between DifCon and DifInt. DifCon equals the difference between baseline and follow-up for the control group, and DifInt equals the difference between baseline and follow-up for the intervention group. Such comparison will give the actual effect size due to the intervention. Generalized linear model (GLM) will be used for analytical purpose, and the models will be adjusted for factors which are different between control and intervention groups at baseline. For the secondary outcomes (motivation to smoking cessation, change in dietary patterns, and physical activity), chi-square tests will be used to detect any associations in the outcome variables across gender, age categories, level of education, and socioeconomic status. The difference in proportion with 95% confidence interval between control and intervention groups will be computed using the test of proportion, and odds ratios (OR) with 95% confidence interval will be computed using logistic regression techniques. The models will be adjusted for covariates as appropriate.

Rasch analysis using RUMM30 software will be used to investigate the psychometric properties of the Health Literacy tool and to compute the overall score from the 12-item HLS-Q12 tool. Individual item, as well as the overall score from all items combined, will be compared for gender, age group, level of education, occupation, and SES using chi-square, *t*-tests, or ANOVA as it is appropriate.

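### The two entry routes pull blood pressure change in opposite directions, and the analysis adjusts for them only if a baseline test happens to flag a difference

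*Protocol article*

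**What the plan says.** - **Entry.** The Inclusion criteria list two routes by blood pressure: untreated at or above 130/80, and treated with "controlled blood pressure defined as < 130/80 using antihypertensive medication for a minimum of 6" weeks. The Participants section is wider: "anyone with SBP ≥130 mmHg and/or DBP ≥80 mmHg and/or self-report use of medication for hypertension will be considered eligible". Under Recruitment, interested people are "assessed for eligibility that includes the measurement of blood pressure".
- **Aim and definition.** The aim is to "investigate if a health education intervention program lowers high blood pressure". The measurement section adds: "Participants will be considered to have high blood pressure if recorded SBP ≥130 mmHg and/or DBP ≥80 mmHg".
- **Primary outcome.** "The primary outcome is the difference in clinical SBP and DBP within and between control and intervention groups".
- **Analysis.** Under Statistical analyses, the effect is a contrast of changes from baseline: "it could be shown as the difference between DifCon and DifInt". It is fitted by a generalized linear model adjusted for factors that differ between the arms at baseline. The Abstract names another method: "Analyses will include analysis of covariance to report the mean difference in blood pressure between the control and the intervention group".
- **Allocation.** Under Cluster randomization and Sequence generation, 18 villages form two blocks of nine. One coin toss decides which block gets the intervention, and the groups are not divided by risk factors for high blood pressure.

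**The concern.** Blood pressure decides entry and is also the outcome. People chosen because a reading was high tend to read lower next time, and people chosen because it was low tend to read higher, with no treatment effect in either case. The concurrent control arm protects the comparison only if both arms contain the same mix of routes. With two randomized units there is little to make the mix equal, and a contrast of raw changes then carries the difference in mix into the estimated effect, in either direction. The within-group change has no such protection: a fall in the intervention arm could be read as benefit when part of it is selection.

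**Working it through.** **The plan's own figures.** The plan gives no figure for this drift. The Sample size section supplies the 5 mmHg target and the SD of 12 mmHg used below. Its 106 per group is not reproduced by a two-sample calculation at two-sided 0.01 and 95% power, which needs 206 per arm. That is a separate matter and nothing here depends on it.

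**Inputs.** From the documents: SD 12 mmHg, SBP cut-off 130 mmHg, 150 per arm. Assumed: population mean SBP 125 to 135, correlation ρ between repeat readings 0.6 to 0.8, difference between arms in the share entering as controlled 10 to 20 percentage points. Selection is modelled on SBP alone, with the selecting reading as baseline.

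**Step 1: drift in each route, no treatment effect.** For a normal variable cut at 130, with z = (130 − mean)/12, φ the normal density and Φ its distribution function:
- drift above the cut-off = −(1 − ρ) × 12 × φ(z)/(1 − Φ(z))
- drift below it = +(1 − ρ) × 12 × φ(z)/Φ(z)

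| Mean | ρ | Above | Below | Gap |
|---|---|---|---|---|
| 125 | 0.6 | −5.2 | +2.7 | 7.8 |
| 125 | 0.8 | −2.6 | +1.3 | 3.9 |
| 130 | 0.6 | −3.8 | +3.8 | 7.7 |
| 130 | 0.8 | −1.9 | +1.9 | 3.8 |
| 135 | 0.6 | −2.7 | +5.2 | 7.8 |
| 135 | 0.8 | −1.3 | +2.6 | 3.9 |

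The drift is −1.3 to −5.2 mmHg above the cut-off and +1.3 to +5.2 below it. The gap between routes is 3.8 to 7.8 mmHg.

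**Step 2: between-arm contrast.** Spurious difference in change = gap × difference in share.
- Equal mix: 0.
- Smallest: 3.8 × 0.10 = 0.4 mmHg.
- Largest: 7.8 × 0.20 = 1.6 mmHg.

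Against 5 mmHg this is 0.4/5 = 8% to 1.6/5 = 32%.

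**Step 3: second set of assumptions.** A simulation with mean 128, between-person SD 15 and within-person SD 5, 8 or 11 (ρ = 225/250 = 0.90, 225/289 = 0.78, 225/346 = 0.65), and 10% versus 30% controlled, leaves 0.5, 1.2 and 2.1 mmHg in the raw difference in change.

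**Step 4: within-arm change.** In the same simulation, with 20% controlled in both arms and no effect, each arm falls by 0.9, 2.1 and 3.6 mmHg. The between-arm difference is 0.

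**Step 5: effect of adjustment.** With mean 130, SD 12, ρ = 0.7 and 10% versus 30% controlled, step 1 gives a gap of 2 × 0.3 × 9.57 = 5.74, so the raw bias is 5.74 × 0.20 = 1.15 mmHg. Simulation gives about the same, and about 0 once baseline SBP, entry route or both are in the model.

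**Step 6: would the baseline tests catch it?** Two-proportion z test, 150 per arm:
- 10% v 30%: z = 4.33, p < 0.001
- 20% v 40%: z = 3.78, p < 0.001
- 10% v 20%: z = 2.43, p = 0.015
- 20% v 30%: z = 2.00, p = 0.046 (about 0.06 with continuity correction)

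**The case against.** The strongest reply is that a randomized control arm under the same entry rules removes regression to the mean from the main contrast, that the Abstract already names analysis of covariance, and that a large imbalance would trigger the protocol's own adjustment. Much of this stands. With an equal mix the bias is zero, baseline adjustment removes nearly all of an unequal mix in these simulations, and step 6 shows that a 20 point gap would be flagged if entry route or medication were tested.

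What does not stand is that the protocol secures any of this. The Abstract does not name the covariate. The Statistical analyses section does not commit to baseline pressure and makes adjustment depend on a test, without naming medication status among the tested characteristics. A 10 point gap can fall on either side of 0.05.

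Three limits on size are fair:
- The Participants section admits anyone reporting medication use whatever the reading. If that rule governs, treated people are not selected on a low reading and the upward drift disappears.
- Recruitment describes an eligibility measurement and then a recording upon enrolment. If these are separate and the second is the baseline, the drift shrinks.
- The Sample size section does not say whether 12 mmHg is the SD of single readings or of change.

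A reader might go further and infer that the trial cannot say whether the programme lowers high blood pressure, because controlled participants do not have it and dilute the effect. The documents do not support that. The definition cited in the Background and the eligibility rule under Participants both count medication use as hypertension, and the hypothesis is to reduce blood pressure, not only readings above 130/80. The share of controlled participants and how much they can gain are unknown. If 10 to 30% gained nothing, 5 mmHg would average 5 × 0.9 = 4.5 down to 5 × 0.7 = 3.5, but both inputs are assumptions.

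**Conclusion.** The point holds as a defect in the adjustment rule and in the definition of the primary effect. It does not invalidate the between-arm comparison. If the mix of entry routes differs by 10 to 20 points, the raw contrast carries about 0.4 to 1.6 mmHg of spurious SBP difference (0.5 to 2.1 mmHg in the second set of assumptions, 10% versus 30%). That is enough to distort a 5 mmHg effect but not to create one of that size. It is zero if the mix is equal and close to zero with fixed baseline adjustment. The within-group change is exposed even with an equal mix: about 1 to 4 mmHg of apparent fall at 20% controlled. These sizes rest on the assumed correlation, mean and mix, on the Inclusion criteria governing entry, and on the selecting reading serving as baseline.

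**What to change.** 1. **Statistical analyses:** name baseline SBP (or DBP) and entry route or medication status as fixed covariates in the primary models, whatever the baseline tests show. This agrees with the analysis of covariance in the Abstract. Medication status is worth having beside baseline pressure because treated and untreated people may drift towards different means.
2. **Primary outcome:** make the baseline-adjusted between-arm difference the sole primary effect, and the within-arm change descriptive only.
3. **Reporting:** give the estimate in participants at or above 130/80 at baseline beside the all-participant estimate, as a supporting result with lower precision. Resting the main conclusion on that subgroup would be a trade-off that this point does not require.
4. **Eligibility text:** reconcile the Participants section and the Inclusion criteria on treated people whose pressure is still high, so that the entry-route variable has a level for everyone enrolled.

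The cost is a few sentences and one extra table. Baseline pressure is already collected, and medication status is needed to apply the entry criteria. Fixed covariates do not cure having only two randomized units. They remove only the part of the imbalance that comes through baseline pressure and entry route.

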### Exclusion criteria

Aged > 75 years of agePregnant womenPeople who have advanced CVDs or have any serious condition that restricts their participation in the studyParticipants will be withdrawn from the study if they are unwilling to continue their participation and withdraw their consent, or any women participants who become pregnant during the study

### Dropout

Participants will be considered as a dropout if they are not willing to continue their participation for any reasons or they withdraw due to health problems or if someone died.

### Implementation of the intervention

#### Intervention

In the intervention arm of 150 participants, the ORCD investigators will form at least ten teams, led by a volunteer leader who will lead the teams and communicate with the project investigator or the doctor if it is necessary. The intervention arm will involve (i) delivering a blended learning education program, including delivering printed materials, and (ii) weekly phone calls to the team leaders. The intervention is an educational program focused on awareness of a healthy lifestyle, including motivation to participate in regular physical activity, community engagement, and keeping frequent contact with health professionals. The chief investigator will keep a record of each team and communicate with the team leaders once every week to remind them to adhere to the intervention program. The weekly monitoring program will continue until the study ends.

The lectures will be delivered to ten teams, comprised of about 15 participants in each team, and will be led by a volunteer team leader using the ORCD’s laptop, overhead projector, and sound system in local clubs, school premises, or participants’ houses. The ORCD investigator, including the physician and an information technology person, will assist with the education programs. Where required, the physician will add interpretations or additional explanations following WHO guidelines and recommendations [41].

#### Control group

The control group will only receive the printed materials at their initial clinic visit.

### Intervention materials (learning materials) for lifestyle modification

The intervention materials will comprise three learning modules: module 1—the effect of high blood pressure on CVDs such as its association with stroke, heart attack and heart failure, kidney diseases, and sexual dysfunction; module 2—managing high blood pressure by managing a healthy weight, taking part in regular exercise, managing stress, consuming a healthy diet including eating of a variety of fruits and vegetables, and avoiding foods high in sodium including raw salt; and module 3—smoking and its associations with cancers and CVDs, and motivation of smoking cessation.

The learning materials will include evidence-based information with pictures, fact sheets, and published literature. The learning materials will be refined following consultation before printing and recording. Ten non-participants, five women and five independent of the study, will be requested to read the learning materials to assess comprehension, wording, and appropriateness. The learning materials will be refined and prepared both in printed version and recorded lectures. The chief investigator will record three modules of about 15 min each, i.e., 45–50 min in total in Bengali language using a video recording software, Camtasia (TechSmith *Camtasia 2019*). Each team leader will be given one Omron blood pressure measuring unit free of cost.

### Interventions that are permitted or prohibited

Participants will receive learning kits and motivational phone calls related to the intervention. The exercise programs will not be supervised but study investigators will facilitate in forming peer groups to take part in various activities as teams. Women will participate as a team of at least five women. The participants will be encouraged not to take part in physical activity alone. In the information sheet provided to the participants, the address of the ORCD and Swinburne’s ethics office will be supplied with information that participants can use to contact if they encounter any serious events. Given the current coronavirus-2019 (COVID-19) situation in the study location (identified as the least affected area in Bangladesh), data collection and intervention delivery will be managed by meeting appropriate social distancing requirements and following government policy using facemask and hand sanitizer to mitigate virus transmission.

### Equipment and blood pressure measurements

Blood pressure will be measured using a calibrated Omron Premium Blood Pressure Monitor Device, Omron HEM-7322 (Australia). Blood pressure will be measured from the right arm with the person sitting upright after 3 min of rest, and a further measurement will be taken following a period of at least 3 min of rest. A third measure will be taken if a major difference is observed between the first two measures and the nearest two measures will be recorded. The two readings will be averaged for SBP and diastolic blood pressure (DBP) separately. Participants will be considered to have high blood pressure if recorded SBP ≥130 mmHg and/or DBP ≥80 mmHg.

### Outcome measures

#### Primary outcome

The primary outcome is the difference in clinical SBP and DBP within and between control and intervention groups. We will report both the absolute difference and the difference in change after follow-up.

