#### Hypothesis

A motivational education program to change lifestyle by smoking cessation, taking part in regular physical activities and managing a healthy diet, and receiving a weekly motivational phone call will reduce blood pressure compared to the control group receiving an information booklet and general advice only.

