### Sample size

A total of 212 participants (106 per group) will provide 95% power at a significance level of 0.01 to detect a difference of 5 mm/Hg in SBP, assuming a standard deviation of 12 mm/Hg. Assuming loss-to-follow of approximately 40% for various reasons, the required number to recruit is 300 participants (150 per group). This sample size was based on previous research, which showed a decrease in SBP of 5 mm/Hg was associated with a clinically significant reduction in the relative risk of stroke and coronary heart disease events [39].

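### The primary outcome is unranked and defined differently in three places: SBP and DBP, within and between groups, absolute difference and change

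*Protocol article*

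**What the plan says.** The definition under Outcome measures, Primary outcome, reads: "The primary outcome is the difference in clinical SBP and DBP within and between control and intervention groups." It continues: "We will report both the absolute difference and the difference in change after follow-up." That covers two pressures, within-group and between-group differences, and two summary measures, with no order among them.

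Other sections describe the primary outcome or its analysis differently:

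- **Abstract, Methods:** "The primary outcome will be the absolute difference in clinic SBP and DBP". The analysis is then given as "analysis of covariance to report the mean difference in blood pressure between the control and the intervention group", together with the difference in change.
- **Hypothesis:** the programme "will reduce blood pressure compared to the control group receiving an information booklet and general advice only", which is a between-group statement.
- **Statistical analyses:** the control-group change is set against the intervention-group change; "it could be shown as the difference between DifCon and DifInt". The section adds: "Such comparison will give the actual effect size due to the intervention." The model is a generalized linear model adjusted for factors that differ at baseline. The section does not say whether SBP or DBP decides.
- **Sample size:** 106 per group for a 5 mmHg difference in SBP, SD 12 mmHg, alpha 0.01, power 95%. DBP is not mentioned. The rationale is again SBP: "This sample size was based on previous research, which showed a decrease in SBP" of that size.

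**The concern.** A primary outcome should fix in advance which result answers the trial's question. Here the reader cannot tell whether SBP or DBP decides, or whether the deciding summary is the 6-month difference or the difference in change.

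The within-group element is the weakest part. It does not test the hypothesis, which is against control. It also mixes any effect of the programme with changes that would occur without it:

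- Untreated participants enter because their blood pressure was raised when measured at recruitment, so some fall on re-measurement is expected.
- Table 1 places baseline in December to March and the intervention and follow-up in May to November, so season and calendar time enter too.

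With an unranked list, a report could lead with whichever element looks best and still be consistent with the Primary outcome section.

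**Working it through.** **1. The plan's own sample size.** Inputs from Sample size: Δ = 5, SD = 12, alpha = 0.01 (taken as two-sided; the article does not say), power 95%.

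- Two-sample comparison: n per arm = 2(SD/Δ)²(z₀.₉₉₅ + z₀.₉₅)² = 2 × 5.76 × (2.576 + 1.645)² = 2 × 5.76 × 17.81 = 205.2, so 206. The exact t calculation gives 207; one-sided z gives 182. None of these is 106.
- One-sample or paired comparison: 5.76 × 17.81 = 102.6, so 103 by z. The exact t calculation gives 106, with power 0.950.

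The printed 106 per group therefore coincides with a within-group change, not with a between-group contrast. This does not prove intent, but it shows that the ambiguity may reach beyond wording. With 106 per arm, between-group SBP power at two-sided 0.01 is Φ(5/(12√(2/106)) − 2.576) = Φ(3.033 − 2.576) = 0.68, before any allowance for clustering.

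**2. What a within-group test would pick up.** The Background reports a 3.9 mmHg SBP fall under usual care in a regional trial. Assume an SD of change of 12 mmHg (the article gives 12 but does not say that it is the SD of a change) and 106 in the arm.

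- Standard error = 12/√106 = 1.166; 3.9/1.166 = 3.346.
- At 0.05: Φ(3.346 − 1.960) = 0.917.
- At 0.01: Φ(3.346 − 2.576) = 0.779.
- With the t distribution: 0.912 and 0.763.

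A fall of that size with no programme effect would usually be significant within the arm.

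**3. SBP or DBP, one contrast each, either may succeed.** Family-wise error = 1 − P(|Z₁| ≤ c and |Z₂| ≤ c), bivariate normal with correlation ρ (assumed; not in the article).

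| Level per test | ρ = 0.5 | ρ = 0.6 | ρ = 0.7 |
|---|---|---|---|
| 0.01 | 1.90% | 1.85% | 1.77% |
| 0.05 | 9.07% | 8.75% | 8.35% |

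**4. The wider list.** This uses 10,000 simulated null trials, 106 per arm, individual-level data, no clustering and no regression to the mean, with SBP–DBP and pre–post correlations of 0.5–0.7 (assumed).

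| Results that may count | 0.05 per test | 0.01 per test |
|---|---|---|
| SBP or DBP change | about 9% | 1.8–2.0% |
| plus absolute differences | 15–16% | 3.5–3.6% |
| plus changes within the intervention arm | 20–21% | 4.6–5.0% |

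**5. Absolute difference versus change.** If baseline pressure is a covariate, modelling follow-up or change gives the same treatment coefficient: subtracting baseline from both sides alters only the baseline slope. The Abstract's covariance analysis names no covariate, however, and the Statistical analyses section adjusts only for factors found to differ at baseline. The article therefore does not settle whether the two summaries coincide.

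**The case against.** The strongest reply is that the article does identify the effect. The Hypothesis is against control, and the Statistical analyses section calls the between-group difference in change the intervention's effect. On that reading the within-group changes are only the two components of that contrast, and regression to the mean largely cancels if the arms are comparable. This stands. A reader might infer from the Primary outcome section that a fall within the intervention arm alone would count as success; the article does not say so.

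A reader might also infer that type I error is uncontrolled at the 5% level. The article does not support that either. The only alpha it attaches to blood pressure is 0.01, and the 95% intervals in Statistical analyses belong to the secondary outcomes. At 0.01 per test, even the full list in step 4 stays near 5% before clustering.

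The size of regression to the mean cannot be fixed from the article. Participants admits people on SBP and/or DBP, and Inclusion criteria also admits medicated participants controlled below 130/80, whose re-measured mean would tend to rise. A figure built on SBP selection alone would overstate the shift for the whole arm. For this reason step 2 uses the article's own usual-care figure. That figure comes from a 24-month trial in people at or above 140/90 mmHg, so it illustrates and does not predict.

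Finally, a multiplicity rule may sit in an analysis plan that is not shown, and sizing on SBP while also naming DBP is common. Both are fair. Neither removes the disagreement between sections of the article over what is primary, and that definition belongs in the protocol.

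**Conclusion.** The point holds as a badly fixed and inconsistent primary definition. The Primary outcome section lists SBP and DBP, within and between groups, absolute and change, without ranking; the Abstract and Statistical analyses sections name different summaries; only SBP is sized.

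The practical size depends on how the list is used. SBP-or-DBP error is about 1.8–1.9% at 0.01 per test or 8.3–9.1% at 0.05, for assumed correlations of 0.5–0.7. A 3.9 mmHg fall unrelated to the programme would be significant within an arm of 106 about 92% of the time at 0.05 and 78% at 0.01, assuming an SD of change of 12 mmHg. The within-group element is therefore uninformative about the hypothesis, whatever level is used. That the definition disagrees between sections rests on the text alone and needs none of these assumptions.

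**What to change.** Define one primary comparison: the between-arm difference in mean SBP at 6 months, adjusted for baseline SBP, at one stated two-sided alpha. Test DBP second in fixed order, or make it the first secondary outcome. Report within-group changes in descriptive tables without p-values. Use the same definition in Abstract, Primary outcome and Statistical analyses, and base the Sample size section on that comparison.

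The definition itself costs only wording and uses data already planned. The small downside is that DBP no longer counts as primary on its own. Basing the sample size on the between-arm comparison would show the gap in step 1 (206–207 per arm against 106), which has to be faced separately. Nor does naming one contrast resolve the design in Cluster randomization, with one randomised cluster per arm and individual-level analysis; that is a separate and larger threat to error control.
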